### Recruitment {15}

Patients will be recruited by health care networks and their affiliated general practitioners (GP) through various means, including (1) face-to-face invitations; (2) phone invitations; (3) promotional materials such as posters, leaflets, and brochures; (4) press releases and newspaper articles; (5) promotion through project website; and (6) promotion through social media. In addition, patients can be recruited by occupational physicians of different companies which will allow us to recruit a heterogeneous group covering a broad spectrum of professions.

### Assignment of interventions: allocation

#### Sequence generation {16a}

Blocked stratified randomization will be used to assign participants to the randomization groups. Strata have been defined by age, gender, type of employment (brain worker/physical worker), and status of disease (acute or Long COVID). Randomization sequence has been generated by the statistical software package STATA, function STRATA rand (StataCorp. 2019. Stata Statistical Software: Release 16. College Station, TX: StataCorp LLC).

#### Concealment mechanism {16b}

The allocation table is stored in the LMS and is queried by an automated script during the registration process. The stratification variables are known, because they are collected via the T0 questionnaire which takes place before the randomization process. In concrete terms, this means that after participants have registered in the LMS with their code, they complete the T0 questionnaire and are then automatically assigned to an intervention group. Thus, additional measures to establish the allocation sequence are not necessary, as no active action is required due to the automatism. Likewise, no measures to conceal the sequence are necessary due to the automation.

#### Implementation {16c}

The computer-generated allocation sequence was transformed into a randomization reference table for each stratum stored in spreadsheet calculation software. Patients register themselves in the LMS. Patients are then sequentially selected for randomization and classified to strata based on the stratification variables. The allocation number is read sequentially from the reference table for the respective stratum.

### Assignment of interventions: blinding

#### Who will be blinded {17a}

Participants themselves are blinded. They only receive the information that they have been assigned to an intervention group called “A,” “B,” or “C.” The participants do not know which measures are possible. They also do not know which intervention portfolio is associated with which letter. GPs are blinded in the way that they are not told which group a patient has been allocated to.

The study management and data analysts themselves are generally not blinded. However, they do not have direct access to participant data and participants during the trial period, and the evaluation is done on aggregated data once the study is completed.

#### Procedure for unblinding if needed {17b}

A process for unblinding is not envisaged, as no incidental diagnoses or other realistic events requiring immediate action by the participant are conceivable in the given conception. Nor would legal demands be likely to make this necessary.

### Data collection and management

#### Plans for assessment and collection of outcomes {18a}

##### Primary outcome

GPs document sick leave days and BEM days in patient records as part of their normal work outside the study. At the end of the trial, the GP totals these days per study participant she enrolled for a period of 6 months counting from the day of registration in the LMS. This registration is defined as the start of the intervention. The GP then writes the accumulated days into a pseudonymized list of her patients and transmits this file to the study center via an end-to-end encrypted virtual data safe access. This simple procedure reduces the workload for GPs and eliminates the need for special instruction.

##### Secondary outcomes

All questionnaires conducted in the trial are collected via integrated html-based forms within the LMS. All data collected via the LMS is stored in the related sql database.

Various dimensions of health are assessed via the PROM-based T0 to T3 questionnaires:

*Health-related quality of life (mental and physical)* is measured via short-form 12 (SF-12). The questionnaire consists of 12 items on general health perception (1 item), physical health (2 items), limited physical role function (2 items), physical pain (1 item), vitality (1 item), mental health (2 items), limited emotional role function (2 items), and social functioning (1 item).

The royalty-free version 1 of the questionnaire was used. By weighting and dependent calculation of the individual values, two scores on physical and mental health-related quality of life are generated according to a complex formula. In this trial, the values are not weighted with the orthogonal factor loadings suggested by the test authors, but with oblique factor loadings. It has been shown that this leads to more consistent results, since the calculation includes an interdependence of physical and mental quality of life [30]. Except for these adjustments, the SPSS rule is used for scoring as suggested in the test manual. The SF-12 is part of the T0, T2, and T3 questionnaires.

*Screening for depression* is carried out by a 9-item PHQ-9 subgroup of the patient health questionnaire family. This subgroup constitutes the depression module and can be used as an independent score to screen for depression. It measures common depression symptoms over a 2-week reference period via 4-point Likert scale with response categories ranging from “Not at all” to “Nearly every day”. Between 0 and 3 points are given for each answer and added up unweighted. The resulting sum score thus ranges from 0 to 27, with higher scores indicating more severe depression symptoms. The PHQ-9 shows good psychometric properties as a screening for depression when using the summed-item method [31, 32]. The PHQ-9 is part of the T0, T2, and T3 questionnaires.

*Physical complaints* are surveyed via the patient health questionnaire 15 (PHQ-15). The questionnaire consists of 15 items on the severity of the most common somatic symptoms. Each item has the 3 response categories “Not bothered at all” to “Bothered a little” to “Bothered a lot” asking about the symptom burden within the last 4 weeks. One of the mentioned symptoms refers to menstrual problems, so this is automatically not presented to male participants. Non-binary participants are presented with the item. In this trial, the PHQ-15 is not evaluated as a score, but as a distribution of symptom frequencies and symptom severity for each symptom recorded. Two of the items (concerning sleep problems and lack of energy) are also part of the PHQ-9. To calculate its score correctly, these two items are asked for a 2-week reference period like in the PHQ-9 instead of a 4-week reference period. The PHQ-15 is part of the T0, T2, and T3 questionnaires.

*Anxiety* is measured via the generalized anxiety disorder questionnaire (GAD-7). The questionnaire consists of 7 items on anxiety symptoms over a 2-week reference period via 4-point Likert scale with response categories ranging from “Not at all” to “Nearly every day”. Between 0 and 3 points are given for each answer and added up unweighted. The resulting sum score thus ranges from 0 to 21, with higher scores indicating higher anxiety. The GAD-7 as a self-report instrument for generalized anxiety disorder has good reliability and construct validity with an optimized sensitivity of 89% and specificity of 82% [33]. There is a high correlation between severity in the GAD-7 and disability scores [34]. The GAD-7 is part of the T0, T2, and T3 questionnaires.

*Burnout (personal, work-related)* is measured via Copenhagen Burnout Inventory (CBI). It divides the symptomatology into personal, work-related, and client-related burnout. Each scale can be calculated independently. All 3 scales show good reliability levels [35]. The questionnaire is administered to check the successful differential diagnosis between burnout and Long COVID. In addition, a possible deviating effect of the MiLoCoDaS intervention plan on varying burnout scores might be discovered. Since the client-related burnout does not essentially affect the research question, this subscale was not included in the survey for reasons of test economy. The chosen subscales consist of 13 items on burnout symptoms using 5-point Likert scales with response categories ranging from “Never / very rarely” to “Always” or from “To a very low degree” to “To a very high degree” respectively. Between 0 and 4 points are given for each answer and added up unweighted. In the resulting sum score, higher values are indicating higher burnout probability. The CBI is part of the T0, T2, and T3 questionnaires.

*Pain* is measured via an adaptation of the Cornell Musculoskeletal Discomfort Questionnaire (CMDQ). In this trial, the CMDQ is not evaluated as a score, but as a distribution of pain locations, frequency, and severity among Long COVID patients. In the first step, the particular pain localization is asked using a suggestion list. Then, the participants rate the pain intensity per previously named region on a numerical analog scale of 1–10, with higher values representing more pain. At last, participants rate the impairment of their usual activities by the reported pain. The German version of the CMDQ shows good psychometric properties [36]. The CMDQ is part of the T0, T2, and T3 questionnaires.

*Social support* is measured via the ENRICHD-Social-Support-Instrument (ESSI), the social support subscale from the Enhancing Recovery in Coronary Heart Disease study (ENRICHD) questionnaire. The questionnaire consists of 5 items on individual availability of social support using a 5-point Likert scale with response categories ranging from “None of the time” to “All of the time”. Between 1 and 5 points are given for each answer. Items are then added up for an unweighted sum score, with higher values indicating greater social support. The ESSI shows good psychometric properties including the German adaptation [37, 38]. The ESSI is part of the T0, T2, and T3 questionnaires.

*Physical fitness* is measured via the 12-item short form of the questionnaire for the assessment of physical function status (FFB-MOT). The questionnaire consists of 12 items on physical activities related to everyday life using a 5-point Likert scale with response categories ranging from “I cannot do this activity” to “I do not have any problems.” Between 1 and 5 points are given for each answer. Items are then added up for an unweighted sum score, with higher values indicating better physical fitness. The FFB-MOT shows good psychometric properties for general populations [39]. The FFB-MOT is part of the T0, T2, and T3 questionnaires.

*Sleep quality* is measured via 5 mixed items on overall assessment of sleep quality, daytime sleepiness, problems falling asleep and staying asleep, and restfulness of sleep. Response categories use 5-point and 6-point Likert scales on quality (overall assessment) and frequency (other terms). Items on sleep problems and restfulness are inverted, so that higher values indicate better sleep. Afterwards, the items’ values are harmonized to a range of 0–100 to equalize the different response scales. Then, an unweighted mean is calculated. A root-based transformation is performed to compensate for ceiling effects and finally standardized to a mean of 66 and standard deviation (SD) of 15. Questions on sleep quality are part of the T0, T2, and T3 questionnaires.

*Work ability* is measured by an abbreviated assessment based on the Work Ability Index (WAI). The original version consists of 7 indicators on (WAI 1) Current work ability compared with the lifetime best, (WAI 2) Work ability in relation to the demands of the job, (WAI 3) Number of current diseases diagnosed by a physician, (WAI 4) Estimated work impairment due to diseases, (WAI 5) Sick leave during the past year (12 months), (WAI 6) Own prognosis of work ability 2 years from now, and (WAI 7) Mental resource [40, 41]. The trial-adapted version consists of 5 items relating to WAI 1, 2, and 4. WAI 4 topic was split into two items that record productivity losses and work quality separately. Items referring to WAI 1 and 4 use a numerical analog scale from 1 to 10; items related to WAI 2 use a 5-point Likert scale with response categories ranging from “poor” to “excellent”. In this trial, the adapted WAI indicators are not evaluated as a score, but as single-item distributions. The described questions on work ability are part of all questionnaires T0 to T3 administered throughout the trial.

*Well-being* is measured via the World Health Organization’s 5-item questionnaire on well-being (WHO-5). The concept of the WHO-5 is based on the Major Depression Inventory, which maps the WHO/ICD-10 criteria for depression. The questionnaire consists of 5 items on general psychological well-being aspects over a 2-week reference period via 6-point Likert scale with response categories ranging from “At no time” to “All of the time”. Between 0 and 5 points are given for each answer. The individual values are added up and multiplied by 4, resulting in a score range of 0–100. Higher values indicate higher well-being. The WHO-5 shows good psychometric properties [42–44]. The WHO-5 also showed a strong negative association with depression symptoms, especially in the range of mild to moderate symptom severity, and is therefore suitable for screening [45]. The WHO-5 is only used in T1 questionnaire.

*Shortness of breath* is measured via 3 specific items using a numerical analog scale from 1 to 10 with pre-COVID-19 and post-COVID-19 values resulting in a total of 6 values. They assess shortness of breath at rest, during light physical activity, and during heavy physical activity. Scores will not be calculated from this. Questions on the shortness of breath are part of the T0, T2, and T3 questionnaires.

*Medication, vaccination status, concentration issues, and COVID-related medical history* are surveyed as single items in order to enable fine-grained subgroup analyses and adjustment for influencing variables. Items on medical history use a numerical analog scale from 1 to 10 with pre-COVID-19 and post-COVID-19 values, if specific symptoms are asked. Scores will not be calculated from this. They are only asked in the T0 baseline questionnaire.

##### Health trackers

Participants from the high-intensity intervention and moderate-intensity intervention groups have health trackers in the form of sliders as a visual analog scale on their overview pages in the LMS. These are labeled as “energy level,” “overall health,” “pain,” “mood,” “amount of enjoyable activities,” and “exercise level” and can be set and saved as often as desired. This offers the possibility of chronological documentation, which allows conclusions to be drawn about the variance of the values referring to the mentioned domains in relation to the individual progress within the therapy program.

##### User statistics

By registering on the LMS, participants agree to their user activity being recorded. The corresponding data is also stored in the participant’s respective data record.

##### Generating data sets

At the end of the trial, all raw values regarding the abovementioned secondary outcome data acquired via the LMS are exported by the platform provider as a data set in .json format (JavaScript Object Notation) and sent to the study management team for evaluation using the end-to-end encrypted virtual data safe. These data sets are pseudonymized without exception. They do not contain any unencrypted personal data.

#### Plans to promote participant retention and complete follow-up {18b}

Participant retention plans are consistent with the strategies to improve adherence to interventions described in {11c}. Full follow-up is usually ensured by adherence to the GP, unless patients generally change their GP. As many of the planned outcomes as possible are collected for all participants, including those who drop out.

#### Data management {19}

The MiLoCoDaS study has a comprehensive data protection conception, including a data protection impact assessment, technical and organizational measures, records of processing activities, and data processing agreements with involved service providers. Data quality assurance has been sufficiently implemented as a requirement of the data protection laws by numerous measures that can be found in the respective documents.

#### Confidentiality {27}

##### General data protection regulations

Throughout the entire project, the data protection regulations according to the GDPR are strictly adhered to and controlled. An accompanying assessment by the responsible department for data protection has been carried out for all relevant aspects. For concrete details on individual measures, please refer to the comprehensive respective documents.

Nevertheless, special reference is made to the constant pseudonymization of patient data at all trial steps.

##### Enrolment and accompanying care

All measures carried out by the GP are subject to medical confidentiality and the data protection standards according to which medical practices are obliged to work. GP keep the pseudonymization key in the patient record, as they are the only party usually holding unencrypted patient data.

##### LMS

Identifying data and health data are stored in different data sets in the LMS database. All health data is stored in pseudonymized form only. Only top-level system administrators of the LMS service provider have direct access to the database. No one else has direct access during or after the study period. However, direct database access during the project period is usually not required. Data exports for analysis exclusively occur in pseudonymized form. The data will be completely anonymized as soon as the purpose and progress of the research permits.

##### Data transfer

Any data transfer between stakeholders that includes the health data of participants will only be conducted in pseudonymized form. When data sets or outcome information is sent, this is done exclusively via end-to-end encrypted password-protected virtual data safe access.

### Plans for collection, laboratory evaluation, and storage of biological specimens for genetic or molecular analysis in this trial/future use {33}

Not applicable, as no biological samples are collected in the MiLoCoDaS study.

### Statistical methods

#### Statistical methods for primary and secondary outcomes {20a}

Generalized linear models will be used to compare the distribution of primary outcomes (sick leave days) in the randomization groups. Link function will be determined based on the observed sample distribution (we expect Poisson or Negative Binomial distribution). Secondary outcomes will be analyzed by Repeated Measurements Analysis of Variance and Mixed Models for Change analysis. Longitudinal response curves will be visualized by graphs showing the marginal estimates in the randomization groups. All statistical analysis will be conducted using the software package STATA (StataCorp. 2019. Stata Statistical Software: Release 16. College Station, TX: StataCorp LLC).

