### Outcomes {12}

#### Primary outcome

Primary outcome is the cumulative sum of sick leave days in patients during the period from enrollment to 6-month follow-up. We compare the high-intensity intervention versus moderate-intensity intervention versus control group. In Germany, every employee requires a medical sick leave certificate. The medical sick leave certificate entitles to 6 weeks of continuous payment of the salary by the employer. Thereafter, for additional 180 days, the statutory health insurance provides 80% of the net salary. Law mandates that employers offer employees with sick leave of longer than 6-week duration the opportunity to participate in a structured employment reintegration program (BEM). In such programs, patients are attempted to be reintegrated into their former jobs in agreement with the occupational health physician, the employer, and the employees’ representative board. The usual process is to gradually increase the weekly job hours and job requirements expressed as a percentage of full employment. Therefore, if a patient takes part in such a program, the sum of days that the participant has spent within an integration percentage stage is used as the primary outcome instead (e.g., 10 working days at 50% equals 5 days on full sick leave). In both cases—sick leave days and reintegration days—the data is reported directly to the study management by treating GPs via their health care networks at once at the end of the trial.

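### The primary model names none of the four stratification factors; if fitted on arm alone it would be conservative and less precise than it need be

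*Protocol article*

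**What the plan says.** Under Sequence generation {16a}: "Blocked stratified randomization will be used to assign participants to the randomization groups". The factors follow: "Strata have been defined by age, gender, type of employment (brain worker/physical worker), and status of disease (acute or Long COVID". Under Concealment mechanism {16b} they are confirmed as baseline data: "The stratification variables are known, because they are collected via the T0 questionnaire which takes place before the randomization process".

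The endpoint accrues only after entry: "Primary outcome is the cumulative sum of sick leave days in patients during the period from enrollment to 6-month follow-up". Its analysis, under Statistical methods {20a}, is given as "Generalized linear models will be used to compare the distribution of primary outcomes (sick leave days) in the randomization groups", followed by "Link function will be determined based on the observed sample distribution (we expect Poisson or Negative Binomial distribution". No covariate is named. The Sample size section {14} uses a single-factor ANOVA with three groups, also without covariates.

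Adjustment is mentioned once, under Secondary outcomes in {18a}. Medication, vaccination status, concentration issues and COVID history at T0 "are surveyed as single items in order to enable fine-grained subgroup analyses and adjustment for influencing variables". That sentence is not tied to the primary model or to the strata.

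On earlier sick leave, the full Work Ability Index has an item on the past year (WAI 5), but "The trial-adapted version consists of 5 items relating to WAI 1, 2, and 4". GPs total sick-leave days from the day of registration in the LMS.

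**The concern.** Blocking within strata forces the arms to be alike on the stratification factors. The arm difference therefore varies less from trial to trial than it would under simple randomisation. A model that leaves the factors out does not know this: it counts the variance between strata as noise and reports a standard error that is too large. Confidence intervals come out too wide, and some of the precision that stratification bought is not used.

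The size depends on how well the strata predict sick leave. Disease status is the most plausible predictor. Under Eligibility criteria {10}, the prevention path requires that the patient is still unable to work at entry and the treatment path does not, while the endpoint starts counting at entry.

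There is also a question of prespecification. The distribution is to be chosen from the observed data, and {17a} says the analysts are generally not blinded. Unless the covariates are fixed somewhere, they become one more choice made after the data are seen.

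**Working it through.** **Plan's own figure.** Inputs from {14}: means 30, 29 and 26 days, SD 10, alpha 5%, power 80%, dropout 25%. The squared deviations from the grand mean of 28.33 sum to 8.667, so with n per arm the noncentrality is n × 8.667/100. At n = 113 this is 9.79, and the three-group F test has power 80.3%. Then 113/0.75 = 150.7, which rounds up to 151 per arm and 453 in total. The stated figure reproduces exactly with no covariates.

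**Effect of leaving the strata out.** Take the high-intensity versus control contrast: 4 days, SD 10, 113 evaluable per arm. The arm-only model reports SE = 10 × √(2/113) = 1.330 days. If balanced strata explain a share R² of the outcome variance, the true SE is 1.330 × √(1−R²). By normal approximation:

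- true level, arm only: 2 × (1 − Φ(1.96/√(1−R²)))
- power, arm only: 1 − Φ((1.96 × 1.330 − 4)/(1.330 × √(1−R²)))
- power, adjusted: Φ(4/(1.330 × √(1−R²)) − 1.96)

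R² is an assumption throughout.

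| Assumed R² | True level, arm only | Reported SE ÷ true SE | SE cut by adjusting | Power, arm only | Power, adjusted |
|---|---|---|---|---|---|
| 0 | 5.0% | 1.00 | 0% | 85.2% | 85.2% |
| 0.05 | 4.4% | 1.03 | 3% | 85.9% | 87.0% |
| 0.10 | 3.9% | 1.05 | 5% | 86.5% | 88.7% |
| 0.20 | 2.8% | 1.12 | 11% | 87.9% | 92.0% |
| 0.30 | 1.9% | 1.20 | 16% | 89.5% | 94.9% |

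Coverage of nominal 95% intervals under the arm-only model rises from 95.0% to 98.1% over this range. At the full target of 200 per arm less 25%, that is 150 completers, power for the 4-day contrast is at least 93% either way.

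**Check with a count model.** Simulation used 2,000 trials per setting, 113 per arm, 16 strata from four two-level factors (assumed), blocks of 6, overdispersed counts with mean 30 and SD 10, and a log-link GLM with Pearson-scaled errors. At R² of 0.05, 0.10, 0.20 and 0.30, the arm-only level was 4.3, 3.0, 3.2 and 2.2%; with the strata in the model it stayed between 4.3 and 5.6%. Power was 90 to 92% on arm alone and 91 to 97% adjusted. The Monte Carlo error on a 5% level is √(0.05 × 0.95/2000), about 0.5 points, so this agrees with the formula.

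**How large could R² be?** For one two-level factor, R² = p(1−p) × (difference/SD)². If 5% of patients were acute and differed by 10 days (both assumed), R² = 0.0475 × 1 = 4.75%. Reaching 20% from that factor alone would need a difference of 10 × √(0.20/0.0475) = 20.5 days.

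**The case against.** The strongest reply is that {20a} is silent on covariates and excludes none. This is a condensed article, a covariate list commonly sits in the SAP, and the article does foresee adjustment for other T0 items. That stands: a reader might infer that the plan decided to omit the strata, and the text does not show this.

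The second reply is that nothing promised is lost. This also stands. A reader might infer that the error bars are misleading or the result invalid, but a test below its nominal level still controls false positives, the estimate is not biased, and the 151 per group was derived without covariates.

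The third is that the size is assumed. The article does not call the four factors prognostic. Its Limitations section expects that prevention patients may be underrepresented, and a rare category explains little variance, as the last calculation shows. At R² = 0 nothing changes.

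The fourth is that the levels presume overdispersion is handled, while {20a} names Poisson as a candidate. With mean 30 and SD 10, an unscaled Poisson model would have a level of about 2 × (1 − Φ(1.96/√(100/30))) = 28%, an error in the opposite direction. That is a separate matter, but it limits where the table applies.

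Finally, a reader might take the absence of prior sick leave as a mistake. The outcome is a count that starts at entry, so it has no baseline value in the usual sense, and counting from registration is the endpoint's definition. Prior sick leave would be an added covariate, not a correction.

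What remains is that factors important enough to stratify on, and known for every patient at allocation, are not named in the model that should use them.

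**Conclusion.** The point holds as a conditional and inexpensive improvement. If the primary GLM is fitted on arm alone with overdispersion handled, its standard error is too large by a factor of 1.03 to 1.20 and its true level is 4.4% down to 1.9%, for an assumed R² between 5 and 30%. The cost at 113 evaluable per arm is about 1 to 5 points of power for the 4-day contrast. With weak strata the effect is negligible. The documents support neither a claim of inflated type I error or bias nor one that planned power is lost. The conclusion rests on an assumed R², on balance across strata being achieved, and on a scaled or negative binomial error model.

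**What to change.** State in {20a} that the primary GLM contains arm, the four stratification factors (age in the categories used for randomisation) and the T0 work-ability item on current ability compared with lifetime best (WAI 1), all fixed before the data are seen. State also that the secondary mixed models include the same strata and the T0 value of the outcome where it was collected. All of these variables are already recorded before randomisation, so the cost is wording only.

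Optional, at small cost: ask each GP to add the participant's sick-leave days in the 6 months before registration to the end-of-trial list, and use that count as a further covariate. This is one more number per participant. It needs a check that the consent and the release from confidentiality cover it. Its value is uncertain for prevention patients, who can enter from 7 days after a positive test, so that most of those 6 months may precede the infection.

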### Sample size {14}

The sample size was calculated for a randomized single-factor ANOVA design with 3 groups without clustering, assuming 30 days of illness (standard deviation of 10 days) during 180 days of follow-up in the control group and a reduction by 4 days for the high-intensity intervention (effect size of Cohen’s *d* = 0.4) and a reduction by 1 day in the medium intensity group. Such reduction was deemed by occupational health physicians as well as general practitioners as clinically highly relevant. Compared to the control group, a power of 80%, a type 1 error probability of less than 5%, and a dropout rate of 25% result in a required sample size or *N* = 151 per group. Thus, we aim to include at least *N* = 453 patients. In order to be able to exclude possible correlations due to socio-demographic variables corresponding to the location of participating practices (in particular rural doctors versus urban infrastructure), the target size is an increased sample size of 600 patients in total (*N* = 200 patients per study arm).

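### Prespecify a robust variance for the sick-leave comparison: model-based negative binomial standard errors hold at the protocol's own mean and SD, but can be too narrow or too wide if many totals sit at 0 or near 180 days

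*Protocol article*

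**What the plan says.** Statistical methods {20a} compares sick-leave days between arms with generalized linear models. It leaves the link function to be settled from the data as observed, and adds: "we expect Poisson or Negative Binomial distribution". The negative binomial is thus one of two expected families. The article names no variance estimator, neither model-based nor robust.

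The outcome is the "cumulative sum of sick leave days in patients during the period from enrollment to 6-month follow-up" (Outcomes {12}, Primary outcome). The GP totals it "for a period of 6 months counting from the day of registration in the LMS" (Plans for assessment {18a}), so the window is the same for everyone and the total has a ceiling. Days in a reintegration program are weighted by percentage, for example "10 working days at 50% equals 5 days on full sick leave", so totals need not be whole numbers.

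The only figures for the distribution are in Sample size {14}, "assuming 30 days of illness (standard deviation of 10 days) during 180 days of follow-up in the control group", with "a reduction by 4 days for the high-intensity intervention". Limitations repeats the mean and SD and calls them an approximation.

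**The concern.** A negative binomial model ties the variance to the mean through one dispersion parameter. A duration inside a fixed window can have a shape that this parameter cannot follow: a group at 0 (back at work throughout) and a group at the ceiling (off work throughout). The maximum-likelihood dispersion then need not reproduce the real variance of the mean, and the model-based standard error inherits the discrepancy.

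At stake are the confidence interval and p-value of the primary comparison, for which Sample size {14} intends a type I error below 5% and 80% power. For a model with arm alone, the estimated means are the sample means under either family, so the point estimate is not affected.

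**Working it through.** **Inputs.** From Sample size {14}: control mean 30, SD 10, arm means 30, 29 and 26, 180 days, 25% dropout, target 200 per arm. Evaluable per arm: 200 × 0.75 = 150. The shares of patients at 0 and at 180 are not in the article; they are assumptions below.

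**The protocol's own sample size.** In a three-group ANOVA the grand mean is 28.33 and the sum of squared deviations is 2.78 + 0.44 + 5.44 = 8.67. With n = 113 per group the noncentrality is 113 × 8.67 / 100 = 9.8 and power is 80.3%. Then 113 / 0.75 = 150.7, rounded up to 151. This matches the stated figure, so mean 30 and SD 10 are the planning inputs.

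**Formulas.** For the log mean in one arm:
- model-based negative binomial variance: (1/μ + α)/n
- true variance, which the sandwich estimates: σ²/(μ²n)
- ratio of standard errors, model-based to true: √[(1/μ + α) / (σ²/μ²)]

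**At mean 30, SD 10.** σ²/μ² = 100/900 = 0.111.
- Normal shape, fitted α = 0.090: √(0.1233/0.1111) = 1.05. Simulated ratio 1.05, type I error 3.9%.
- Gamma shape, fitted α = 0.076: √(0.1093/0.1111) = 0.99. Simulated ratio 1.00, type I error 4.4%.
- Bounded beta-binomial (realised SD 11): simulated ratio 1.03, type I error 4.6%.

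Across repeated simulations at these inputs type I error was 3.9–5.7%. The negative binomial is adequate here.

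**Assumed shapes.** Two arms of 150, no true difference, mean about 29. Totals are a gamma variable (shape 1.2) capped at 180, plus fixed shares at 0 and 180. Nominal level 5%. Ranges cover repeated simulation runs.

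| Share at 0 / at 180 | Model-based SE ÷ true SE | Type I error |
|---|---|---|
| 10% / 5% | about 0.9 | about 8–9% |
| 10% / 10% | about 0.83 | about 11–12% |
| 20% / 5% | about 1.06 | about 4% |
| 30% / 5% | about 1.2 | about 2% |
| 40% / 8% | about 1.27 | about 1.5% |

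With 10% at 0 and only 2% at 180 it is about 4%; with 20% and 3%, about 3%. The SDs in the 10/5, 10/10, 30/5 and 40/8 rows are 40.5, 51.7, 43.6 and 50.1.

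**Why it goes both ways.** Zeros push the fitted dispersion up, while a few totals at the ceiling raise the real variance more than the dispersion.
- 40% at 0, 8% at 180, the rest exponential (mean 29.9, SD 51.1): fitted α = 5.01, against σ²/μ² = 2.92. The standard error is too wide (simulated ratio 1.28, type I error 1.8%).
- Short absences averaging 15 days plus 5% at 180 (mean 23.3, SD 36.7): 1/μ + α = 0.043 + 0.748 = 0.791, against σ²/μ² = 2.48. Ratio √(0.791/2.48) = 0.56; simulated 0.57, type I error 27.9%. This is an extreme case with almost no zeros.

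**Fractional totals.** Ratios with half-day against whole-day values: 1.05 and 1.05 (normal, SD 10), 0.97 and 0.98 (gamma, SD 30), 1.30 and 1.28 (mass at both ends). No material effect.

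**With a sandwich variance.** Over 20 shapes the ratio of estimated to true standard error was 0.96–1.02. Type I error was 4.3–6.1% in 19 of them and 7.5% in the most skewed (short absences averaging 10 days plus 3% at 180).

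**If Poisson were chosen instead.** At the protocol's own inputs the model-based ratio is √(30/100) = 0.55, and type I error is 2 × [1 − Φ(1.96 × 0.55)], about 28%. The sandwich corrects this as well.

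**The case against.** Four points can be made for the plan as it stands.

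1. *The article fixes no variance estimator.* That detail commonly sits in the full protocol or the analysis plan, neither of which is shown. This stands. A reader might infer that the plan commits to model-based standard errors or has wrongly left out a robust variance; the text supports neither.

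2. *The damaging shapes are not the protocol's.* They have an SD of about 40–50 against the stated 10. At such an SD the planned 4 days would be a standardised effect of 4/40 = 0.10 to 4/50 = 0.08 rather than 0.4, and the sizing would be the larger worry. This stands, and it makes the point conditional. Inflation within the gamma-based shapes appeared only with few zeros and at least 5% at the ceiling, while Discussion describes patients who are not wholly incapacitated and Eligibility {10} excludes hospitalised and repeatedly specialist-treated cases.

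3. *The negative binomial is not a commitment.* It is one of two expectations, and the choice follows the observed data. A reader might take it for the plan's fallback; the sentence does not say so.

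4. *Fractional days.* A reader might suppose that non-integer totals break the error bars. The half-day comparison shows that they do not.

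What remains is that the real shape is unknown and SD 10 is an approximation. The treatment path in Eligibility {10} does not list employment or current sick leave as a condition, while the prevention path requires continuing incapacity, so zeros and mixed profiles are possible. The primary outcome makes provision for absences beyond six weeks. Background {6a} cites about one in five people with Long COVID unable to work and 105 sick days a year in severe cases. Those groups are broader or sicker than this trial's, but they show that long absences occur.

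**Conclusion.** The point holds in conditional form. Both expected families ignore the ceiling on the sick-leave total. At mean 30 and SD 10 this is harmless for the negative binomial. If many totals sit at 0 or near 180, its model-based test can run at about 8–12% (10% at 0, 5–10% at 180) or at about 1–2% (30–40% at 0), with other mixes near 5%.

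These sizes rest on assumed shares, 150 evaluable patients per arm, a comparison of two arms without covariates, and model-based standard errors, which the article does not state. The stronger conclusion, that the planned negative binomial analysis gives wrong error bars or that the stated type I error is already lost, is not supported: the protocol's own figures give close to nominal results.

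This is a cheap improvement. Its value is that the type I error no longer depends much on a distribution nobody has seen yet.

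**What to change.** In Statistical methods {20a}, keep the generalized linear model for the mean and add one sentence: standard errors, confidence intervals and tests for the primary comparison use a robust (sandwich) variance, whichever family is used. Optionally, also report the difference in mean days between arms with its 95% confidence interval, the scale on which Sample size {14} and Limitations express relevance.

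The cost is one sentence and one option in the Stata command. For a model with arm alone the estimate does not change; only the interval and p-value do. The downside is slightly less precise inference if the chosen family happens to be exactly right, and type I error may still run somewhat above 5% under extreme skew (7.5% in the worst shape tried). No change to sample size or data collection is needed.
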